### Coalition recruitment

We will recruit 68 coalitions from community anti-drug coalitions across Pennsylvania and Missouri, USA. This coalition population is similar to other US coalitions, which enhances study generalizability. These coalitions have received funding from a wide variety of sources, and their activity levels have fluctuated with changes in funding levels over time. Coalitions function in rural, suburban, and urban areas, ranging in age from 1 to 30 years old. We connect with these coalitions through the Evidence-based Prevention and Intervention Support (EPIS) group in the Pennsylvania State University’s Prevention Research Center. The EPIS team interfaces with community agencies, schools, and coalitions to provide support to those attempting to integrate prevention research into their practices.

We are using a layered targeted strategy to recruit coalitions, first with email communications from EPIS TA staff. We then introduce the project at coalition regional meetings organized by EPIS, providing time for questions and small group discussion to connect project researchers with coalition members. We then conduct follow-up phone calls and online meetings. The decision to participate rests on each coalition’s leadership team or at times with the full coalition.

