### Randomization

Matched pairs of coalitions will be randomly assigned to the Coalition Check-Up condition or TA as usual. Coalitions will be matched on level of TA availability at baseline (0 = none, 1 = occasional trainings and group TA, 2 = regularly scheduled group TA, 3 = group TA and regularly scheduled one-on-one supervision, 4 = regularly scheduled one-on-one capacity-building TA), years in operation, coalition model employed, population density, US Census poverty rate, and availability of funding. A random number seed will be generated by an external third party using random.org. SAS Proc Surveyselect uses this random number seed to select one of each pair of coalitions recruited into the study as the intervention condition. Data collectors and data analysts will be blind to study condition, with no circumstances under which unblinding is permissible.

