#### Aim 2: Measures—EBP implementation

EBP implementation consists of three core facets assessed annually: (a) quantity. (b) quality, and (c) sustainability. EBP quantity is a coalition-level variable computed as the number of youth reached annually by all coalition-supported EBPs. To estimate the total number of youth reached by a particular EBP, we ask the coordinator of the EBP to report the unduplicated number of youth reached annually at each location where the program is being implemented. Thus, EBP quantity represents the sum “reach” achieved by complementary programs implemented by a coalition to address different developmental stages across the prevention spectrum.

EBP quality is a coordinator-reported program-level variable computed as a composite of 7 scales: (a) staff training (6 items, α = .91); (b) staff motivation and competence (5 items, α = .93); (c) fidelity monitoring (11 items, α = .76); (d) evaluation (13 items, α = .81); (e) dosage (2 items); (f) adherence (7 items); and (g) implementation barriers (11 items, α = .81) (21, 26).

EBP sustainability consists of two measures: (1) overall EBP sustainability and (2) sustainability planning. Overall EBP sustainability is a coalition-level variable that is the sum number of years all EBPs are in operation during years 2–4 of the project, including both existing and new EBPs. An EBP will be designated as non-operational when (a) it has no reach or (b) there is an absence of ongoing training or TA in the past 12 months and no funding available to support the program. Sustainability planning is a coordinator-reported program level outcome (12 items, α =.85) [57].

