### Power analysis

We used Optimal Design to estimate power for cluster-randomized trials [60]. In this study, youth-level substance use data and program-level implementation data are clustered within coalitions, which is the level of random assignment. Overall, we will have a power of .80 to detect Cohen’s *d* effect size ranges as follows: aim 1, .24 to .37, a small to medium effect, depending on the measure of coalition capacity; aim 2, .31 to .42, a medium effect, depending on the EBP implementation measure; and aim 3, .25, a small effect, for measures of youth substance use.

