Building from models of the Coalition Check-Up’s overall effects on youth substance use, we will test whether EBP implementation mediates between the experimental condition and youth substance use. We will test the EBP implementation measures described in Aim 2 (quantity, quality, sustainability) in separate mediation models. Each model will test for both direct and indirect effects on youth substance use—aggregate 30-day use, and aggregate lifetime use measures of alcohol, tobacco, marijuana, and opioids. If a mediational pathway is significant, we will conduct follow-up analyses modeling each of the specific substances separately [63, 64].

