Each study aim is well-positioned to make important contributions to the implementation science literature. The first aim contributes knowledge of how the Coalition Check-Up affects coalition capacity, by operationalizing the pathway from the prevention support system (TA) to the prevention delivery system (EBP implementation) in the Interactive Systems Framework. These analyses are an important step toward understanding how the Coalition Check-Up might work to support positive outcomes for youth in communities. This knowledge will also help providers and policy makers understand critical components of the prevention support system. Findings will provide guidance on how the prevention support system can best build capacity to address youth substance use in communities across the country.

The second aim will show how the Coalition Check-Up does or does not contribute to aspects of EBP implementation. By examining the Coalition Check-Up as a strategy to support the adoption and integration of EBPs into community settings, we can clarify pathways that improve participant outcomes and benefit population health. Such work is important in not only establishing the evidence for this coalition-driven TA system, but also for understanding the relations between the prevention support system and the prevention delivery system as outlined by the Interactive Systems Framework. Analyses will provide empirical evidence on key implementation processes that support EBPs according to the Interactive Systems Framework.

The third aim will provide insight into how to reduce youth substance use. A granular understanding of how the Coalition Check-Up and EBPs in the prevention delivery system can reduce youth substance use will strengthen evidence bases for both the Interactive Systems Framework and the Coalition Check-Up. By understanding how EBP quantity, quality, and sustainability relate to youth outcomes, policy makers and funding agencies can make better decisions about where to focus scarce EBP dissemination and implementation resources. Furthermore, TA providers will be better able to direct coalitions towards EBP approaches that maximize impact on youth substance use. By reflecting the imperfections of real-world practice, our findings will be more generalizable than in studies where coalitions and EBPs are well funded.

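### Separate mediation models cannot tell EBP quantity from overall EBP sustainability, which sum over the same programs; add a joint model before any statement on which facet matters

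*Protocol article*

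**What the plan says.** The Aim 3 mediation plan is explicit: "We will test the EBP implementation measures described in Aim 2 (quantity, quality, sustainability) in separate mediation models". Each model examines direct and indirect effects on aggregate 30-day use and aggregate lifetime use. No model with more than one facet is described.

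The facets are defined under Aim 2: Measures—EBP implementation. Quantity is a coalition-level count of youth reached in a year, added up over all EBPs that the coalition supports. Overall sustainability is a coalition-level sum of the years that all EBPs operate during project years 2–4. The two are also tied by rule: "An EBP will be designated as non-operational when (a) it has no reach". Quality is of another kind: "EBP quality is a coordinator-reported program-level variable computed as a composite of 7 scales". Sustainability planning, the second sustainability measure, is likewise a program-level scale.

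Objectives and aims and Aim 2: Plan of analysis both hypothesise that the intervention raises quantity, quality and sustainability. The Discussion states the intended use, which concerns limited resources: "By understanding how EBP quantity, quality, and sustainability relate to youth outcomes, policy makers and funding agencies can make better decisions about where to focus".

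**The concern.** Quantity and overall sustainability both grow with the number of active programs, so they will be correlated within arm. When condition shifts both and only one acts on youth use, a model containing only the other still shows a path from condition to mediator and a path from mediator to outcome. The second path is borrowed from the omitted facet. Each separate model can show that a facet, taken alone, lies along the pathway. None can show which of the two carries it.

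At stake is the facet-level reading in the Discussion. A funder could be told that keeping programs running longer lowers youth use when the effect came from the number of youth reached, or the reverse. The tests of the overall Aim 3 effect are not affected.

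**Working it through.** **Inputs from the article.** The trial has 68 coalitions ("We will recruit 68 coalitions from community anti-drug coalitions across Pennsylvania and Missouri, USA"), and randomisation is used to "select one of each pair of coalitions recruited into the study as the intervention condition", so 34 per arm. Power analysis says "we will have a power of .80 to detect" the listed effects, including "aim 2, .31 to .42, a medium effect, depending on the EBP implementation measure". It gives no power or error rate for the mediation tests.

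**The stated detectable effect.** For a coalition-level outcome without covariate adjustment, at two-sided 5% (assumed), the detectable d at power .80 is about (1.96 + 0.84) × √(2/34) = 0.68, or 0.69 with t quantiles. Reaching .31 to .42 needs a variance factor of (.31/.69)² = .20 to (.42/.69)² = .37. The intraclass correlation, cluster size and covariate R² that would supply this factor are not given, so the figure can be neither reproduced nor refuted. The point does not depend on it. Two cases bracket the effect on the mediators: d = .69 (power about .80 for that path) and unadjusted d = .42 (power about .40).

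**Overlap implied by the definitions.** The measures were built as defined, assuming a mean of 2 to 6 EBPs per coalition, a coefficient of variation of reach of 0.3 to 1.0, and 80% yearly survival of a program. Quantity and overall sustainability then correlate at .67 to .96. Either one correlates at about 0 with mean program quality. These assumptions give programs in every coalition the same reach distribution; differences in catchment size would lower the correlation.

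**Error rate in separate models.** Assumptions: two facets, both raised by d; residual correlation r; only the first acts on the outcome, with standardised path b = .4. A facet is declared a mediator when both paths have p < .05. Given condition, the null facet has partial correlation rb with the outcome, so with 65 residual degrees of freedom the expected statistic is

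t = rb√65 / √(1 − r²b²).

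- r = .3: .12 × 8.06 / .993 = 0.97; chance of p < .05 about .16
- r = .5: .20 × 8.06 / .980 = 1.65; about .38
- r = .7: .28 × 8.06 / .960 = 2.35; about .65

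Multiplying by .80 (d = .69) gives .13, .30 and .52. Multiplying by .40 (d = .42) gives .065, .15 and .26. Repeated simulations agree: 12–13%, 28–30% and 50–53% at d = .69, and 5–7%, about 15% and 25–26% at d = .42.

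**Error rate in a joint model.** The null facet's second path is now tested at 5%, so the rate is about .80 × .05 = 4%, or .40 × .05 = 2%. In simulations with three facets, d from .42 to 1.0 and b of .3 or .5, it stayed between 2% and 5%.

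**Cost in power for the true facet.** In the joint model, t = b√(64(1 − r²)) / √(1 − b²) = 3.49√(1 − r²). At d = .69:

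| r | t | chance of p < .05 | × .80 |
|---|---|---|---|
| .7 | 2.49 | .70 | .56 |
| .85 | 1.84 | .45 | .36 |
| .95 | 1.09 | .19 | .15 |

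In the separate model, power for the true facet is about .74. With three mutually correlated facets the loss is larger: at r = .7 and b = .3, from .54 to .28.

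**The case against.** The strongest objection concerns causal order. Programs that stay in operation plausibly produce reach. If sustainability acts through reach it is a genuine mediator, and a parallel-mediator model would hide it. In a simulated chain of that kind (path .5 to .85), separate models detected sustainability in 31–66% of trials and the joint model in about 4%. This stands. It is why the separate models should be kept and why the joint model needs its no-causal-order assumption stated.

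The joint model's power is also low where the overlap is strongest. That stands too, but it means that 68 coalitions carry little information for separating these two facets. The separate models do not supply that information; they only leave the gap unseen.

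It is also fair that the stated Aim 3 test is whether EBP implementation mediates, that the Discussion speaks of how facets relate to outcomes and does not name a winner in advance, and that this is a follow-on analysis. These limit the weight of the point. The Discussion still invites a reading facet by facet.

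A reader might infer more than the article supports:

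- That all three facets overlap by construction. Quality and sustainability planning are program-level scales, not sums over programs, so any correlation with quantity would be empirical.
- That the plan double-counts a shared pathway. It nowhere adds indirect effects across models.
- That quality enters Aim 3 as an unweighted mean that ignores program size. The article does not say how quality is brought to coalition level, and a full plan may.

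**Conclusion.** The point holds for quantity against overall sustainability. Separate models are fixed in the text, the definitions tie the two measures together, and the plan has no analysis that can tell them apart. At correlations near .7, towards the low end of what the definitions imply under the assumed program counts and reach spread, a facet with no effect of its own is credited in roughly a quarter (d = .42) to a half (d = .69) of trials, against 2–5% in a joint model.

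These sizes rest on values that the article does not give: two-sided 5% tests, linear coalition-level models, b = .4, and the listed values of d and r. At r = 0 the rate is only 2–4%. The excess arises only if the intervention moves the null facet, the facets are correlated, and another facet truly affects youth use.

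A reader might conclude that the trial cannot say which facet matters. That is true of the planned analysis but not settled for the data: all facets are collected, and a joint model might or might not separate them. This is an inexpensive improvement to a secondary analysis, not a threat to the main Aim 3 tests.

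**What to change.** 1. Keep the separate models and describe them as tests of each facet taken alone.
2. Add one coalition-level model with quantity, quality and overall sustainability entered together. Include sustainability planning, or state why it is left out.
3. Report the combined indirect effect through all facets. It does not require splitting the shared part between them.
4. Base any statement about which facet carries the effect on the joint model, and qualify the Discussion sentence to match.
5. Report the observed correlation between quantity and overall sustainability. State that at about .7 or more 68 coalitions may not separate them, and that the joint model assumes no causal order between facets.

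No new data are needed. The costs are some analysis work, wider intervals and lower power per facet in the joint model, and a more modest claim if the facets prove inseparable.

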### Cost tracking

Throughout the project, we will assess coalition activity costs to understand the resources necessary for Coalition Check-Up implementation. This assessment will use methodology developed in prior work including annual average cost estimates as well as ranges of costs across differing coalition settings [66]. We will adopt an ingredients-based approach where all program inputs and activities in the day-to-day implementation are identified regardless of whether a direct cost was required [67]. We will seek cost information from multiple sources. Where available, project budgets indicate amounts for personnel and non-personnel inputs. For personnel costs, we will use Coalition Check-Up time allocation measures developed for this project as part of the TA Record [68]. When costs are not apparent (e.g., in budgets), we will derive estimates based on opportunity cost or market value of the resource. Including such valuations enables creation of a range of cost estimates, where the lower bound excludes opportunity costs and the higher bound reflects the value of non-budgeted resources. This process will set the foundation for cost-effectiveness analyses pursued in future projects.

### Dissemination and data sharing

To make results available to both scientists and practitioners, we will pursue presentations at scientific meetings, presentations to community coalitions, brief reports and press releases on the EPIS website (http://epis.psu.edu/), and publication in peer-reviewed journals. Upon request, we will share de-identified data from published studies with interested investigators once they have IRB approval.

## Discussion

This innovative trial tests a unique approach to supporting community coalitions’ implementation of EBPs. Other low-cost TA models are typically expert driven and specific to a single type of coalition [16]. In contrast, the Coalition Check-Up supports coalition-driven action planning. Unlike existing TA models, the Coalition Check-Up can also be applied broadly across coalition models because it focuses on common dimensions of coalition capacity and EBP implementation linked to youth outcomes [20, 21]. The proactive, data-driven monitoring in this study involves continuous quality improvement cycles that identify TA needs and provide timely support to improve capacity [69]. The Coalition Check-Up is unique in its use of motivational interviewing to support its audit and feedback implementation strategy, thereby strengthening the collaborative working relationship, enhancing coalition-driven action planning, and coalition commitment to making change [70, 71].

Using the Interactive Systems Framework and an extensive history of coalition research, this study will examine causal pathways from TA to EBP implementation and youth outcomes [22, 24, 26]. In this way, the study advances the field of implementation science by providing new evidence of the relationship between Interactive Systems Framework domains and implementation outcomes. The scale of this project allows for longitudinal testing of mediating pathways from Coalition Check-Up to distal community-wide outcomes. Together, these innovations will yield evidence about not only if but also how the Coalition Check-Up works. Advancement of the Coalition Check-Up evidence-base will encourage model usage as a low-cost and generalizable approach for supporting coalitions to achieve community-wide reductions in youth substance use.

Each study aim is well-positioned to make important contributions to the implementation science literature. The first aim contributes knowledge of how the Coalition Check-Up affects coalition capacity, by operationalizing the pathway from the prevention support system (TA) to the prevention delivery system (EBP implementation) in the Interactive Systems Framework. These analyses are an important step toward understanding how the Coalition Check-Up might work to support positive outcomes for youth in communities. This knowledge will also help providers and policy makers understand critical components of the prevention support system. Findings will provide guidance on how the prevention support system can best build capacity to address youth substance use in communities across the country.

The second aim will show how the Coalition Check-Up does or does not contribute to aspects of EBP implementation. By examining the Coalition Check-Up as a strategy to support the adoption and integration of EBPs into community settings, we can clarify pathways that improve participant outcomes and benefit population health. Such work is important in not only establishing the evidence for this coalition-driven TA system, but also for understanding the relations between the prevention support system and the prevention delivery system as outlined by the Interactive Systems Framework. Analyses will provide empirical evidence on key implementation processes that support EBPs according to the Interactive Systems Framework.

The third aim will provide insight into how to reduce youth substance use. A granular understanding of how the Coalition Check-Up and EBPs in the prevention delivery system can reduce youth substance use will strengthen evidence bases for both the Interactive Systems Framework and the Coalition Check-Up. By understanding how EBP quantity, quality, and sustainability relate to youth outcomes, policy makers and funding agencies can make better decisions about where to focus scarce EBP dissemination and implementation resources. Furthermore, TA providers will be better able to direct coalitions towards EBP approaches that maximize impact on youth substance use. By reflecting the imperfections of real-world practice, our findings will be more generalizable than in studies where coalitions and EBPs are well funded.

### Limitations

A potential challenge of this project is keeping the coalitions engaged in the Coalition Check-Up and focused on the development and implementation of action plans addressing prioritized areas for growth. Success in this regard may depend on a strong relationship between the TA provider and the coalition, which we include in our fidelity monitoring protocol. TA use of motivational interviewing should help in promoting a strong relationship and in encouraging coalitions to implement their action plans [72].

Another problem could be lower than expected participation in Pennsylvania Youth Survey or the Missouri Student Survey. If we identify school districts in participating communities without student data, a new data collection incentive plan will provide financial incentive for missing school districts to participate in data collection. We will discuss with the state-level survey sponsors to see what logistical support we can offer schools in missing districts.

### Conclusion and impact

Results are expected to have a positive impact on the field by establishing the evidence-base for a low-cost, broadly applicable TA model supporting sustained implementation of evidence-based drug prevention programs and policies.

## Data Availability

Please contact the lead author for more information.

## Abbreviations

EBP: Evidence-based practices
EPIS: Evidence-base Prevention and Intervention Support project
PROSPER: PROmoting School-community-university Partnerships to Enhance Resilience
TA: Technical assistance
